### Randomisation and concealment

Computer-generated randomisation will be stratified on a 1:1 allocation by site, baseline aerobic exercise capacity (% predicted VO_2peak_), physiological stage (B or C), age, and sex (female, male), per Fig. 1. An independent statistician/staff member will employ randomisation by minimisation to allocate participants. Where possible, site assessors will be blinded to participant group allocation and identification. Participants’ data and identification will be stored centrally (REDCap™) and accessible only by a trial coordinator (uninvolved in participant enrolment, randomisation, or assessment). Unblinding is expected to occur in the event of a serious adverse or adverse event. Participants are not blinded owing to the nature of the intervention (exercise).

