Behavioural, physical, and psychological factors contributing to decreased exercise and PA participation and capacity in congenital heart populations are manifold, including advice to avoid exercise [11, 12], reduced confidence to exercise [13], poor self-perception of exercise capacity [14], as well as low lean tissue/adiposity ratio [15], impaired muscle oxidative capacity and strength [16], impaired ventilatory and cardiopulmonary responses to exercise [17, 18], and decreased neurocognitive function [19–22]. However, the risk of adverse events during exercise is very low in people with congenital heart conditions. A recent systematic review reported no progression of symptoms, heart failure, or death, among the 403 participants reviewed [23].

Preliminary findings suggest that adults with congenital heart conditions tolerate and obtain benefit from appropriately prescribed exercise in gym-based programmes [24, 25], including improvement in aerobic exercise capacity and cardiac output [26–28], muscular function [29], and quality of life [30]. However, these studies have been limited by short duration (~ 12 weeks), design (non-randomised), and small sample size (< 50 participants).

To date, there are no randomised controlled trials testing the physiological and neurocognitive response to telerehabilitation treatment in adults with varying biventricular pathologies. Home-based cardiac rehabilitation is a viable treatment for clinically stable CVD patients [31]. Studies have shown telehealth-delivered exercise to be accessible and cost-effective in CVD patients [32, 33]. A possible means to reduce the financial impact associated with monitoring and rehabilitation of adults with chronic heart failure has been the judicious use of telehealth [34]: a recent study found potential to reduce costs associated with travel to attend medical appointments when replaced by telehealth delivery [35], and another study found equivalent care could be provided for lower cost [36]. The lack of larger, longer-duration high quality randomised controlled trials which redress lower rates of access and participation via innovative telerehabilitation and investigate the effect of exercise in adults with congenital heart pathologies prevents definitive exercise prescription as a treatment option for this cohort [37–39].

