## Methods

### Trial design

This will be a multi-site, two-armed, parallel-group, single-blind, superiority randomised controlled trial investigating the physiological and psychological effects of a telehealth-delivered 16-week aerobic and resistance exercise intervention in a biventricular congenital heart cohort, employing pre- and post-intervention measurements, with an 8-month follow-up.

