### Adherence, compliance and activity monitoring

Adherence and compliance to exercise training will be monitored digitally (HR device, attendance at Zoom™ sessions) as well as via analog (training logs). Attending 80% of the prescribed sessions—with attendance to > 70% of sessions in the 4 weeks preceding the follow-up assessment visit—is considered adherence to the intervention. Attendance of 20–79% of the prescribed sessions are semi-adherent participants. Non-adherent participants are those that attend < 20% of the prescribed sessions. Compliance is defined as those participants who have worked for > 50% of the session at or above the target intensity. Compliance is reported for aerobic and resistance training per session. Sessional compliance requires meeting the target training criteria for aerobic and resistance training. During the intervention and the 8-month follow-up period, intervention participants are contacted monthly to monitor adverse events and change in PA levels.

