## Adverse events/serious adverse events

Adverse events (AE) such as the occurrence of an adverse medical symptom and serious AEs such as death, hospitalisation, or progression of symptoms according NYHA classification will be recorded in REDCap™ and reviewed every 12 weeks from commencement of recruitment. Enrolled participants will be provided with a procedure to follow in the event of the onset of adverse medical symptoms during either an unsupervised aerobic or supervised telehealth resistance training session. Exercise professionals conducting the telehealth resistance training sessions will be trained in the appropriate process in the event of either an AE or a serious AE. A data safety and monitoring board comprising members independent of the trial with no competing interests and including clinical experts and a biostatistician will be created to ensure the process to be followed by recruits and/or staff during the intervention and in case of the occurrence of an AE or serious AE as well as to recommend cessation of the trial to lead investigators if necessary (AE or serious AE). Further roles and responsibilities of the board will be outlined in its charter, and the board will meet every 3 months to review trial progress, conduct, and AEs/serious AEs. Reports on trial progress will be filed with participating site governance bodies annually as well as to the trial sponsor and funding body.

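### Unblinding is expected after any adverse event, serious or not, and the rule does not keep the assessor of the primary exercise test blinded

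*Protocol article*

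**What the plan says.** Trial design calls the study a "multi-site, two-armed, parallel-group, single-blind, superiority randomised controlled trial". Randomisation and concealment states that participants are not blinded, because the intervention is exercise. The one role it names as blinded is the assessor: "Where possible, site assessors will be blinded to participant group allocation and identification". It then sets the rule at issue: "Unblinding is expected to occur in the event of a serious adverse or adverse event". It names no recipient and does not require that anyone's task depend on knowing the arm.

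The section on adverse events shows how wide the trigger is: "Adverse events (AE) such as the occurrence of an adverse medical symptom and serious AEs such as death, hospitalisation, or progression of symptoms", the last judged by NYHA class. The same section sets up an independent data safety and monitoring board.

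On surveillance, the adherence section says that "intervention participants are contacted monthly to monitor adverse events and change in PA levels", and the Controls section gives the control arm the same monthly contact. Only the intervention arm also has live resistance sessions over Zoom (Resistance training protocol), run by staff trained to respond to events.

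The primary outcome is VO2peak from a ramp-protocol cycle CPET, measured at baseline, 16 weeks and 12 months (Outcomes, Table 4).

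**The concern.** In a single-blind trial with open-label participants, assessor blinding is the main safeguard against differential handling of the outcome test. A rule that lifts it for any symptom gives that safeguard away easily. The article states no reason why the person running the CPET should learn the arm when a participant reports an event. The participant already knows it, the exercise staff know it because they run the sessions, and a separate board reviews safety.

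The primary endpoint is a performance test. I take it as general knowledge, since the article does not say so, that encouragement and the decision to end the test can influence a measured peak. An assessor who knows the arm could therefore shift the result, even without intent. At stake are the credibility of the primary comparison and the single-blind label.

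**Working it through.** **1. Whose blind can be broken?** Set the named roles side by side:
- Participants: not blinded.
- Exercise professionals: they deliver the sessions, so they know the arm.
- Trial coordinator: controls access to data and identities, and takes no part in enrolment, randomisation or assessment.
- Site assessors: blinded where possible.

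By elimination, the only stated blind that unblinding can break is the assessors'. This is an inference from the named roles; the sentence itself names nobody.

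**2. Is surveillance equal?** Table 3 gives 6 + 42 = 48 resistance sessions, which are the supervised ones. The 6 + 12 + 12 + 18 = 48 aerobic sessions are unsupervised. Monthly contact over 16 weeks is about 4 occasions in each arm. That makes about 48 + 4 = 52 occasions to notice an event in the exercise arm and about 4 in control. With equal true event rates, more events could still be recorded in the exercise arm. The article does not trace how an event seen on Zoom would reach the site assessor.

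**3. The planned precision.** The article claims at least 90% power with 100 participants for a 10% difference at two-sided 5%, with 10% drop-out. It gives no standard deviation (SD), so the figure cannot be reproduced, only inverted:

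largest SD = 10 / [(1.960 + 1.282) × √(2/n)]

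This is 15.4 points with 50 per arm and 14.6 points with 45 per arm. For illustration I take SD 14.6 and n = 45, so SE = 14.6 × √(2/45) = 3.08 points.

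**4. Illustrative bias (all inputs assumed).** Let pE and pC be the shares of exercise and control participants tested by an unblinded assessor, and b the shift in VO2peak per such test, 2 to 5 points.
- If assessors favour exercise (raise that arm, lower control), bias = b × (pE + pC).
- If they shift every unblinded test the same way, bias = b × (pE − pC).
- With no true effect, type I error = Φ(−1.96 + bias/SE) + Φ(−1.96 − bias/SE).

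| pE / pC | Bias, favouring exercise | Type I error | Bias, same direction | Type I error |
|---|---|---|---|---|
| 10% / 10% | 0.4–1.0 | 5.2–6.2% | 0 | 5.0% |
| 20% / 10% | 0.6–1.5 | 5.4–7.8% | 0.2–0.5 | 5.05–5.3% |
| 30% / 30% | 1.2–3.0 | 6.8–16.4% | 0 | 5.0% |
| 50% / 20% | 1.4–3.5 | 7.4–20.6% | 0.6–1.5 | 5.4–7.8% |

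Worked entry, 20% / 10% with b = 5: bias = 5 × 0.30 = 1.5; 1.5 / 3.08 = 0.487; type I error = Φ(−1.473) + Φ(−2.447) = 0.070 + 0.007 = 7.8% before rounding of the parts.

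**5. What the table shows.** When assessors favour exercise, bias follows the sum of the two shares, so 30% / 15% and 22.5% / 22.5% both give 0.45 × (2 to 5) = 0.9 to 2.25 points. Unequal unblinding is not needed for harm. It is needed only under the same-direction pattern.

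**6. Timing.** Only events before the 16-week visit can affect the 16-week test. Later events can affect only the 12-month test.

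**The case against.** The strongest reply is that the sentence does not say the assessor is told. Disclosure to a clinician, the coordinator or the board would also fit, and the coordinator is kept apart from assessment. Who may be unblinded, and how, may be set out in the full protocol (Version 9) or the board's charter, neither of which is shown. This stands as far as practice at the sites goes. It does not rescue the sentence: the article states a rule, with a very wide trigger, and the only blinded role it names is the assessor. If someone else was meant, the sentence should say so.

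A reader might also infer more than the text supports:
- That events are likelier with exercise. No section says this; the Introduction says "the risk of adverse events during exercise is very low in people with congenital heart conditions". Only denser detection is supported.
- That unblinding will concentrate in the exercise arm. This is possible, but monthly contact is identical in both arms and the route from Zoom session to assessor is not described.
- That self-rated NYHA worsening counts as a serious event. Self-assessment belongs to an outcome row in Table 4; the adverse-event section refers only to NYHA classification.
- That the bias has a known size. Every rate and shift used above is assumed.

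It is also fair that blinding is promised only where possible, and that open-label participants may vary their own effort in any case. The Discussion cites self-administered online tests, quality procedures and standardised training. The CPET is not a self-administered online test, and the other two measures do not address knowledge of allocation.

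**Conclusion.** The concern holds in limited form. The stated rule expects unblinding after any adverse event, does not restrict who learns the allocation, and so leaves the assessor of the primary test exposed without a stated safety need. Denser detection in the exercise arm means that unblinding may differ by arm, but the concern does not depend on that.

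The size is undetermined. Under the assumed shares and shifts above, with SD 14.6 points and 45 per arm, bias runs from 0 to 3.5 points against the planned 10%, and type I error from 5.0% to 20.6%. If events before week 16 are rare, the effect is small: at 5% unblinded in each arm and b = 5, it is 5 × 0.10 = 0.5 points. The conclusion rests on reading the assessor as the person unblinded and on the CPET being open to assessor influence. It should be corrected; it is not evidence that the result will be biased.

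**What to change.** Replace the sentence with a rule to this effect: outcome assessors remain blinded after an adverse or serious adverse event; allocation is disclosed only to the treating clinician, the safety reviewer or the data safety and monitoring board, and only where their task needs it.

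Record every instance of assessor unblinding, by arm and by timing (before the 16-week or before the 12-month test), and report the counts. An analysis without the affected tests may be added, but only as a cautious sensitivity check. It conditions on an event after randomisation that may differ by arm, so it can introduce selection bias of its own.

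The cost is a wording change, one log field and some care in keeping event information away from CPET staff. That care is hardest at small sites; Table 2 gives one site 15 participants. Recruitment began in June 2022 and was expected to run to the end of December 2024, so some tests will predate any change. The new rule still protects the outstanding ones, and the log can document past instances where they are known.

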**Fig. 1 Fig1:**
[figure not shown]
The Congenital Heart Fitness Intervention Trial (CH-FIT) study design flow chart

### Flow of participants (recruitment to completion) and schedule

Figure 1 presents the study design flow chart of participants, and Table 1 lists the schedule of recruitment, consent, enrolment, assessments, randomisation, intervention, and follow-up periods. The recruitment period is expected to last for approximately 30 months, with an expected monthly rate of recruitment commensurate with each site’s participant allocation (generally 3–4 participants per month across all sites). In addition, sites will over-recruit by up to 10% in order to achieve sufficient participant enrolment to attain the required adequately powered sample size.

**Table 1 Tab1:**
[figure not shown]
The Congenital Heart Fitness Intervention Trial (CH-FIT) schedule of visits (Tables 3 and 4 )

For each trial site, the target sample size is summarised in Table 2.

**Table 2 Tab2:** Participant numbers (intervention and control) per trial site

Site name	Intervention telehealth (*n*)	Control (*n*)	Total (*n*)
Royal Prince Alfred Hospital (RPAH)	17	18	**35**
Royal Melbourne Hospital (RMH)	13	12	**25**
Prince Charles Hospital (PCH)	8	7	**15**
Fiona Stanley Hospital (FSH)	12	13	**25**
**Total (** ***n*** **)**	**50**	**50**	**100**

## Intervention

The telerehabilitation intervention comprises unsupervised moderate-to-vigorous intensity aerobic training combined with telehealth-delivered supervised resistance training, summarised in Table 3 (either one continuous aerobic and resistance session or two separate sessions according to participant preference).

**Table 3 Tab3:** Excluding warm-up and cool down of ~ 10 min (total time is approximately 30–40 min per individual session)

Weeks (sessions)	Intensity category	Objective intensity	Subjective intensity
**Aerobic exercise training progression**			
1–2 (6)	Moderate	40–50% HRR	4 OMNI-RES Scale
3–6 (12)	Moderate	50–60% HRR	5 OMNI-RES Scale
7–10 (12)	Vigorous	60–70% HRR	6 OMNI-RES Scale
11–16 (18)	Vigorous	70–80% HRR	7 OMNI-RES Scale
**Resistance exercise training progression**			
1–2 (6)	Moderate (moderate load)	60% 1RM (3 sets, 8–12 repetitions)	4–5 OMNI-RES Scale
3–16 (42)	Vigorous (moderate-to-high-load)	70% 1RM (3 sets, 8–12 repetitions)	6–7 OMNI-RES Scale

### Aerobic training protocol

Participants will receive a heart rate (HR) monitor transmitting real-time exercise intensity data to an electronic device enabled with the Polar Flow Mobile App™. Additionally, participants will be asked to record per-session exercise duration and per-session average and peak HR as well as rate of perceived exertion (RPE) according to the OMNI-RES scale. Participants will be instructed by qualified exercise professionals on how to achieve exercise intensity commensurate with progressive target levels. Self-selected aerobic exercise modalities may include either indoor or outdoor walking/jogging/running, dancing, cycling, skipping, stepping, or any other form of continuous aerobic exercise sustained within the prescribed HR reserve (HRR) or RPE range (see Table 3) to be performed for 30 min, including 5 min each of warm up and cool down, three times per week. Participants will receive a complimentary gym membership to facilitate adherence to unsupervised aerobic exercise training.

### Resistance training protocol

Participants will be provided with a resistance exercise device (Gymstick™): a cylindrical fibre-glass rod of 1300 mm length and 30 mm diameter. At each of the stick, interchangeable flexible rubber tubes of varying resistance are attached with the other end of the tube looped at either of feet or hands. Qualified exercise professionals will instruct participants on the correct use of the device and how to achieve desired intensity on a progressive basis as well as supervise small group resistance training sessions via Zoom™. Training sessions will comprise three sets of 8–12 repetitions of 6 resistance exercises at targeted and progressing percentage intensities of one repetition maximum (1RM) three times per week (see Table 3) for approximately 40 min per session including 5 min each of warm up and cool down. Participants will be educated on appropriate breathing during each phase of the resistance exercises and shown how to avoid the Valsalva manoeuvre. If onset of symptoms, fatigue, or inability to complete a set of resistance exercises at the lowest resistance level or bodyweight occurs, longer intra-set and inter-set rest periods will be permitted.

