### Power analysis and statistical measures

A sample size of 100 is predicted to have ≥ 90% power (two-sided *α*: 5%) in estimating a VO_2peak_ difference of 10% between intervention and control (primary outcome), as suggested by preliminary findings [41]. We assume a 10% drop-out for a 16-week duration. Generalised linear mixed models with random subject and site effects (to control for variation between individuals and the clustering effects of site) and group-time interactions will be used to estimate the between and within group pre- and post-intervention changes in the primary outcome, controlling for covariates that may influence the outcome. Results will be summarised using descriptive and inferential statistics, with relevant *P* values (significance < 0.05). Sensitivity analysis of per-protocol vs intention-to-treat will be conducted. We will handle missing data by imputation using the closest match method. i.e. substitute a same time-point value from a participant with the closest value for the measured variable at other time points [42].

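### Small-group training in the intervention arm only has no counterpart in the stated primary model, so the treatment standard error may be somewhat too small

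*Protocol article*

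**What the plan says.** The Protocol article, under Resistance training protocol, has qualified exercise professionals instruct participants and "supervise small group resistance training sessions via Zoom", three times a week. Table 3 gives 6 + 42 = 48 resistance sessions over 16 weeks. The Intervention section makes the aerobic component unsupervised. The Controls section leaves the comparator in routine clinical care, with no sessions and no trainer.

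Under Power analysis and statistical measures, the primary analysis is a generalised linear mixed model with "random subject and site effects (to control for variation between individuals and the clustering effects of site") and arm-by-time interactions. No training-group or trainer effect is named.

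The same section says "A sample size of 100 is predicted to have ≥ 90% power" for a "difference of 10% between intervention and control (primary outcome), as suggested by preliminary findings", and adds "We assume a 10% drop-out for a 16-week duration". It gives no SD, ICC, group size or design effect.

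**The concern.** Delivery by shared trainers in shared sessions can make the outcomes of intervention participants resemble each other. Nothing comparable can arise among controls. This is a partially nested design, with clustering in one arm only.

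The article recognises clustering and names site as the source to control. It does not name the source that its own delivery creates. Allocation is 1:1 and balanced by site (Table 2: 17/18, 13/12, 8/7 and 12/13), so a random site intercept is common to both arms and largely cancels from the treatment contrast. Variance between training groups or trainers within the intervention arm does not cancel.

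At stake is the precision reported for the primary outcome. A standard error that omits a real variance component is too small, so the confidence interval is too narrow and the P value too low. The random effects are listed explicitly, so this is a stated choice rather than a detail passed over in a condensed text.

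**Working it through.** **Inputs from the article.** 100 participants, 50 per arm; two-sided 5% test; power at least 90%; a 10% difference in VO2peak; 10% drop-out, hence 50 × 0.9 = 45 evaluable per arm.

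**Inputs that must be assumed.** Training groups of m = 5, stable and non-overlapping; ICC of 0.01, 0.05 or 0.10; total variance held constant.

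**Step 1: the plan's own figure.** It cannot be reproduced, because no SD is given. The SD that yields exactly 90% can be back-solved:

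- 45 per arm: d = (1.960 + 1.282) × √(2/45) = 0.683, so SD = 10/0.683 = 14.6% of the mean.
- 50 per arm: d = 3.242 × √(2/50) = 0.648, so SD = 10/0.648 = 15.4%.

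With 45 per arm, power is 97.7% at an SD of 12%, 92.3% at 14%, 88.5% at 15% and 84.2% at 16%.

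**Step 2: add clustering in one arm.**

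- Design effect in the intervention arm: DE = 1 + (m − 1) × ICC.
- Variance factor of the contrast: F = (1 + DE)/2. The true standard error is √F times the modelled one.
- Error of the nominal 5% test when the component is omitted: 2 × P(Z > 1.960/√F).
- Power with the correct standard error, starting from exactly 90%: P(Z < 3.242/√F − 1.960).

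| ICC (m = 5) | DE | F | √F | Test error | Power, normal | Power, t |
|---|---|---|---|---|---|---|
| 0.01 | 1.04 | 1.02 | 1.010 | 5.2% | 89.4% | 87.1% |
| 0.05 | 1.20 | 1.10 | 1.049 | 6.2% | 87.1% | 84.2% |
| 0.10 | 1.40 | 1.20 | 1.095 | 7.4% | 84.1% | 80.6% |

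The last column uses a noncentral t with Satterthwaite degrees of freedom. It includes the price of estimating a variance from only 45/5 = 9 groups. At ICC = 0 the standard error and test error are unchanged. Across m = 3 with ICC 0.01 to m = 8 with ICC 0.10, √F runs from 1.005 to 1.162 and normal-approximation power from 89.7% to 79.7%.

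**Step 3: how much slack would absorb this.** Power stays at 90% if the SD is no more than 14.63/√F: 14.63/1.049 = 13.9% at ICC 0.05, and 14.63/1.095 = 13.4% at ICC 0.10. The article does not allow a reader to say whether the SD is above or below these values.

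**Step 4: how stable the groups could be.** The section on flow of participants expects 3 to 4 recruits a month across all sites, so 1.5 to 2 a month enter the intervention arm. Sixteen weeks is about 3.7 months, so some 1.5 × 3.7 = 5.5 to 2 × 3.7 = 7.4 participants are in training at once nationally. Stable groups of 5 fit that poorly, and groups of 8 exceed it. Changing membership is more plausible, though the article does not say how groups are formed.

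**The case against.** The strongest reply is that the effect is probably small. VO2peak is measured individually, aerobic training is unsupervised with a self-chosen activity and individual heart-rate targets, and resistance load is set from each person's own maximum. Rolling entry weakens any fixed-group structure. All of this points to a low ICC and stands. It does not remove the point: the same professionals also instruct participants on reaching aerobic intensity (Aerobic training protocol), so a trainer effect can reach that component, and changing groups do not dilute it.

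Three stronger readings are tempting and are not supported.

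- *Power falls below 90%.* The claim is at least 90%, the SD is missing, and a modestly smaller SD would absorb the loss. Sites may also over-recruit by up to 10%. If that adds to the 100 randomised, it offsets the ICC 0.05 case (1.10/1.10 = 1). It would restore power but would not correct a standard error that omits the component.
- *The 5% test is certainly anti-conservative.* If the programme affected nobody, trainers and groups could hardly create correlation through delivery. Inflation mainly needs real effects that differ between groups or trainers and average to zero. The too-narrow interval is the more general consequence.
- *Large trainer caseloads make the problem severe.* The article gives no number of trainers and no rule assigning participants to them, so no such figure has a basis in the text.

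Nor does the model treat participants as fully independent. It has a site effect, which would absorb part of the correlation if groups form within site.

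Finally, group formation and a sensitivity analysis may be described in the full protocol or analysis plan, which are not shown. That is fair for those details. The random effects themselves are stated here.

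**Conclusion.** The point holds in a limited form. Small-group, trainer-led delivery exists in one arm only, and the stated random effects have no term for it. If outcomes or effects vary by group or trainer, the standard error of the primary contrast is somewhat too small. Under the assumptions above (45 evaluable per arm, stable groups of 5, ICC 0.01 to 0.10), the true standard error is 1.0 to 9.5% larger than the modelled one. The low end is the more plausible for this outcome.

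The article's figures neither establish nor exclude a material effect, and they do not show that the stated power is missed. This is an inexpensive improvement to the plan, not a demonstrated error in its conclusion.

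**What to change.** 1. For each intervention participant, record the main trainer and the training group. If membership changes, record session membership instead; attendance at the Zoom sessions is already monitored (Adherence, compliance and activity monitoring). This should start now, since it may be hard to reconstruct later.
2. State how training groups are formed, their usual size and the number of trainers.
3. Pre-specify a partially nested analysis of the primary outcome, at least as a sensitivity analysis: a random trainer or group effect in the intervention arm only, acting on the visits after training begins, with small-sample degrees of freedom.
4. State the SD behind the power figure, and show power over a range of assumed ICCs.

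The cost is one or two data fields, an additional model and slightly wider confidence intervals. With few trainers or shifting groups, the added variance will be estimated imprecisely and a single group identifier may not be definable. That is a reason to accept the sensitivity-analysis form.
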